**15.4. Adverse Events Assessment Criteria**

In this clinical trial, adverse events are all undesirable medical findings that cause symptoms not observed before the start of the clinical trial are classified as adverse events. Expected side effects are also classified as adverse events, and the severity of adverse reactions is classified into mild, moderate, and severe, and they are reported using the ‘Preferred term’ and ‘System organ class’ of MedDRA.

**15.5. Expected Adverse Events and Precautions**

**15.5.1. Expected Adverse Events**

- Pain
- Nausea
- Vomiting
- Abdominal tenderness
- Edema
- Abdominal cramping
- 1-3 degree burns
- Internal tissue thermal damage
- Leg and hip pain
- Vaginal bleeding more than before treatment
- Sciatic nerve injury
- Abdominal and pelvic organ damage (bladder, uterus, intestine, etc.)
- Pain that does not respond to drugs
- Urinary tract infection
- Urination disorders
- Fever due to infection
- Hypersensitivity reactions to the use of contrast agents (dizziness, nausea, vomiting, itching, urticaria, burning sensation, blood pressure drop, heartbeat abnormality, dyspnea, kidney disease, acute renal failure, etc.)
- congestive changes in the abdominal muscles on MR examination

(Limited to cases where there is a scar on the abdomen and the procedure is performed after applying a scar patch.)

**15.5.2. Precautions for Use**

ALPINION Medical Systems Co., Ltd. 35/45

Protocol No. APM-03 Version 1.10/Date 20180103

Subject Safety Information

① Correctly identify and enter subject data.

② Do not use the system until you are familiar with its operation.

③ To prevent overheating of the image transducer, the image should be fixed when not viewing the image.

④ Ensure that no acoustic output is emitted from the system when the image transducer is not in use. Otherwise, the image transducer may overheat.

⑤ When the system is not in use, the image transducer must be fixed or the sound output must be turned off.

⑥ Do not use the system with a defibrillator. This system does not contain any ECG components with defibrillator protection.

⑦ Make sure that the disinfectant does not come into contact with the subject. If the disinfectant comes into contact with the skin or mucous membrane of a subject, it may cause infection.

- Precautions for Applications
  - To avoid system damage and serious subject injury, do not use damaged or defective image transducers.

② Do not bend or pull the image transducer cable as it may damage the image transducer.

③ Use only approved coupling gels.Use of non-approved gels may damage the image transducer and void the warranty.

④ Do not drop the image transducer.Always store the image transducer in a safe place when not in use.

⑤ Use the image transducer with care, as using a damaged or defective image transducer may cause unexpected electric shock.

⑥ Ensure that no sound output is emitted from the system when the image transducer is not in use.

Otherwise, the image transducer may overheat.

⑦ When the system is not in use, the image transducer must be cooled or the sound output must be turned off.

⑧ Always inspect the image transducer used for sharp edges or rough surfaces to avoid serious subject injury.

⑨ Proper cleaning and sterilization of the image transducer is essential to prevent disease transmission. Infection control procedures should be followed.

⑩ Do not use an image transducer sheath which has expired.

⑪ Using a lubricated condom as an envelope may damage the image transducer.

⑫ Do not let the coupling gel get into the eye (or the subject's eye).

⑬ If the gel gets into your eyes, rinse well with clean water.

**15.6. Reporting Adverse Events**

**15.6.1. Adverse Event Training**

ALPINION Medical Systems Co., Ltd. 36/45

Protocol No. APM-03 Version 1.10/Date 20180103

The principal investigator educates sub-investigators and subjects or their representatives on any adverse events that may occur after surgery or use of investigational medical device. Training is provided to report all phenomena that appear after use through the reporting form specified within the time limit specified in the protocol.

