|  | ☞ Patients who have received CT, MRI, or ultrasound images from the hospital where adenomyosis was first diagnosed, or a diagnostic image or report from the hospital where they are currently being treated can also be enrolled. |
| Study Method |  |
|  |
|  | 2. Those who voluntarily sign the consent form and satisfy all inclusion/exclusion criteria will be enrolled in this study and assigned a subject number. |
|  |  |
|  | 3. Subjects enrolled in the study schedule the procedure and receive the scheduled procedure on the day of the procedure. |
|  | Pre-procedure preparations and procedures follow the standard procedures of the institution. |

ALPINION Medical Systems Co., Ltd. 3/45

[figure not shown]

[figure not shown]

Protocol No. APM-03 Version 1.10/Date 20180103

[figure not shown]

1. After the procedure, the operator acquires an image of the treatment area through ultrasound and MRI to check the planned volume and the range of the treatment volume, and observes for any adverse reactions including changes in the skin.
2. After 1 to 2 hours of monitoring in the recovery room, if there are no abnormalities, the patient can be discharged on the same day or the following day.
3. Efficacy and safety are evaluated at one month and three months after the procedure, and the clinical trial is terminated if there are no abnormalities in the subject's body.

The study is expected to take approximately 28 months, including approximately 25 months of subject enrollment after obtaining clinical trial protocol approval from the Ministry of Food and Drug Safety (MFDS) and 3 months of follow-up.

Clinical Trial Period

Even after the clinical trial is completed, it is expected to take approximately 3 months in addition for data processing, statistical analysis, clinical study report preparation and IRB approval.

Subjects can be enrolled in this clinical trial only if they meet all of the following inclusion criteria.

1. Adult female of at least 20 years of age
2. Pre-menopausal or peri-menopausal (FSH<40mIU/ml)
3. Adenomyosis is clinically diagnosed through MR or US imaging
4. Pain score on the Dysmenorrhea Score is at least 4 points

- Dysmenorrhea Score

1 = Not at all (no symptoms)

2 = A little bit (slight symptoms)

3 = Somewhat (few symptoms)

Inclusion Criteria  4 = A great deal (considerable symptoms)

5 = A very great deal (a lot of symptoms)

1. Have not received any other treatment for adenomyosis within 3 months before HIFU procedure

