**11.5. Observation Items, Clinical Laboratory Tests and Observation Method**

<Clinical Trial Schedule Table>

[figure not shown]

|  | Screening | Procedure day | Follow-up period | |
| --- | --- | --- | --- | --- |
| Visit day | Visit 1 | Visit 2* | Visit 3 | Visit 4 |
| Days passed | Day -30 to 0 | Day 0 | Month 1 | Month 3 |
| Visit window | - | - | ± 2 weeks | ± 2 weeks |
| Observation type | Clinic visit | Day surgery | Clinic visit | Clinic visit |
| Hospitalization |
|  |  |  |  |
| Obtain consent | √ |  |  |  |
| Inclusion/Exclusion criteria | √ |  |  |  |
| Demographic surveyl | √ |  |  |  |
| Vital signs2 | √ | √ |  |  |
| Physical examination3 | √ |  |  |  |
| Medical history survey4 | √ |  |  |  |
| ECG test5 | √ |  |  |  |
| Laboratory test6 | √ |  | √ |  |
| FSH | √ |  | √ |  |
| Pregnancy test7 | √ |  |  | √ |
| MRI8 | √ | √ | √ | √ |
| U/S9 | √ | √ | √ | √ |
| Dysmenorrhea Relief Score10 |  |  | √ | √ |
| Dysmenorrhea Score 11 | √ |  | √ | √ |
| Menorrhagia Score 12 | √ |  | √ | √ |
| SF36-v213 | √ |  | √ | √ |
| UFS-QoL (including SSS)14 | √ |  | √ | √ |
| US-guided HIFU procedure |  | √ |  |  |
| Subject satisfaction with procedure15 |  | √ |  |  |
| Adverse event/Serious |  | √ | √ | √ |
| adverse event16 |  |
| Concomitant drugs17 | √ | √ | √ | √ |

1. Demographic survey

Basic information of subjects including date of birth, sex, height and body weight

1. Vital signs

Body temperature, blood pressure (systolic/diastolic), pulse, respiration rate

ALPINION Medical Systems Co., Ltd. 20/45

[figure not shown]

[figure not shown]

Protocol No. APM-03 Version 1.10/Date 20180103

[figure not shown]

1. Physical examination

Appearance, skin, head/neck, chest/lung, heart, abdomen, urinary/genital, extremities, musculoskeletal system, nervous system, lymph nodes, other body organs

1. Medical history survey

Survey of medical history during the past 1 year

1. ECG test

Electrocardiography is performed as a screening test for the procedure. If an abnormality is found on the electrocardiogram, the subject cannot be enrolled in this clinical trial.

1. Laboratory test

Laboratory tests are performed on all subjects to evaluate their overall health, and the test items are as follows.

■ Hematology: Hemoglobin, Hematocrit, RBC count, WBC count with differential, platelet

count

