1. Adverse event/Serious adverse event

Assess according to the criteria defined in Section 16 of the Protocol and record on the Adverse Event/Serious Adverse Event record form in the CRF.

1. Concomitant drugs

Drugs that may affect the results of the clinical study are prohibited, and all drugs already being taken due to underlying diseases are recorded at the time of Screening. Only the drugs added thereafter are recorded in the CRF.

- After the procedure on Visit 2, the subject can be discharged from the hospital on the day of the procedure or hospitalized for about one day according to the judgment of the investigator and the standard procedure of the hospital.

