1. Based on the selected area, the following HIFU irradiation method can be configured in detail.
   - Focal Point Grid: The spacing (X, Y) between points and the Cartesian (lattice) and Cylinder (cylinder) type focal point placement can be configured.

- - Acoustic Power : Acoustic Power (Intensity)
  - PRF (Pulse Repetition Frequency) : Number of irradiation per second
  - Duty : The duration of the irradiation is configured in units of percentage in the time interval between irradiation.
  - Exposure Time : Duration of irradiation on one focal point
  - Point to Point : Travel time between points
  - Cooling Time : Travel time between slice images
  - Generate Points: A focal point is automatically created in a pattern of Cartesian (lattice) and Cylindrical (cylindrical) in the desired area.
  - Add Point: You can manually create focal points that do not have a uniform pattern in a desired area one by one.

1. Based on the treatment plan of the subject set in the preceding step, simulation is performed before actual treatment to check the validity of the treatment plan.
2. Pre-targeting is performed to test the accuracy of the HIFU irradiation before treating the subject. In pre-targeting, the user arbitrarily sets the location to be irradiated, and actually irradiates the HIFU weakly to check its accuracy through the irradiation location information.

- Treatment Procedure

The operator performs HIFU treatment according to a pre-established treatment plan, and observes the necrosis of the lesion and the progress of treatment through ultrasound images and software. If the position of the uterus is shifted due to urine filling in the bladder, adjust the treatment position and start again. Upon completion of the planned treatment of the entire site, a record of the entire treatment is kept in the subject record.

- After Treatment

When the treatment is completed according to the initially set treatment range, the surgeon acquires an image of the treatment area through ultrasound and MRI to check the planned volume and the range of the treatment volume, and observes for any adverse reactions including changes in the skin. Subjects may be discharged from the hospital on the day of treatment or the next day if there is no abnormality after observing the passage of 1 to 2 hours in the recovery room, and fill out a questionnaire about satisfaction with the procedure before discharge.

1. **Follow-up Period <Visit 3, 4>**

■ Visit 3 (1 month after treatment)

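### No contact is scheduled between discharge and Visit 3 (about day 16 to 44), and Section 15.6.1 relies on a subject reporting form and time limit that the protocol does not give

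*Protocol*

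**What the plan says.** The synopsis allows the subject to leave early if nothing abnormal is seen: "After 1 to 2 hours of monitoring in the recovery room", "the patient can be discharged on the same day or the following day". Section 11.6.2 agrees: "Subjects may be discharged from the hospital on the day of treatment or the next day if there is no abnormality". The note on Visit 2 under the schedule table in Section 11.5 gives the alternative to same-day discharge, which is to be "hospitalized for about one day according to the judgment of the investigator and the standard procedure of the hospital".

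The Section 11.5 schedule table sets the visits as "Days passed | Day -30 to 0 | Day 0 | Month 1 | Month 3", with "Visit window | - | - | ± 2 weeks | ± 2 weeks". The adverse event row is ticked at Visits 2, 3 and 4 only. Physical examination is ticked at screening only, and vital signs at screening and the procedure day only.

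Section 15.6.1 has the principal investigator educate both sub-investigators and subjects (or their representatives). It continues: "Training is provided to report all phenomena that appear after use through the reporting form specified within the time limit specified in the protocol".

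The expected events in Section 15.5.1 include pain, nausea, vomiting, edema, cramping, burns, urinary tract infection and "Fever due to infection". For each expected event, Section 15.6.2 has the investigator enter the name, onset and resolution dates, severity, causal relationship, treatment and outcome in the CRF.

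**The concern.** Safety is half of the stated objective, and Section 12.3.1 gives a single safety endpoint that covers every adverse event. The trial has one arm, so the reported event rates stand alone, with no comparator observed under the same ascertainment. How well events are captured therefore matters directly for what can be said about safety in the new indication.

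Between discharge and Visit 3 the protocol depends on subjects coming forward. The sentence meant to organise this points to a time limit that a subject cannot find in the protocol. A short-lived event after discharge that a subject does not volunteer would be dated and graded from memory at Visit 3. A more serious late event would reach the 24-hour reporting route of Section 15.6.3 only once the site had heard of it.

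**Working it through.** **Step 1: length of the interval without scheduled contact.** Inputs: Visit 2 is day 0; Visit 3 is Month 1 with a window of ± 14 days (Section 11.5 table). The protocol does not convert a month to days, so the month length is an assumption.

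- Earliest Visit 3 = month length − 14; latest = month length + 14.
- 30-day month: 30 − 14 = day 16; 30 + 14 = day 44.
- 28-day month: day 14 to day 42. 31-day month: day 17 to day 45.
- In weeks, for the 30-day month: 16/7 = 2.3 and 44/7 = 6.3.
- With discharge on day 0 or day 1, the interval after discharge runs from 16 − 1 = 15 days to 44 − 0 = 44 days, nominally 29 to 30 days.

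About six weeks is therefore the upper limit of recall and about four weeks the nominal value.

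**Step 2: what is scheduled inside that interval.** Neither the Section 11.5 table nor the visit descriptions in Section 11.6.2 contain a call, diary or interim visit between Visits 2 and 3. Subject diaries are mentioned once, in a general list of source documents in Section 17.4.1, and in no schedule or visit.

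**Step 3: can the reference in Section 15.6.1 be resolved?** The forms and limits in the protocol are:

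- Section 11.5, note on adverse events: an adverse event record form in the CRF, which is a site document.
- Section 15.6.2: CRF entries made by the investigator, with no time limit.
- Section 15.6.3: a serious adverse event record sheet, with a limit of 24 hours from investigator to sponsor. Events suggesting significant risk that the investigator considers serious or possibly device-related go to the sponsor immediately.
- Section 15.6.3: 7, 8 and 15 days for onward reporting of serious or unexpected events to the IRB and the ministry.

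For staff and serious events, the reference in 15.6.1 resolves. For a subject reporting to the site, no form and no time limit is given. For ordinary non-serious events, no time limit is given for anyone.

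**Step 4: what Visit 3 can recover without the subject's memory.** Visit 3 has MRI, ultrasound, blood tests and FSH. These may show tissue or organ injury still present. They would not recover an episode of pain, vomiting, cramping or fever that has already resolved. No physical examination or vital signs are scheduled at Visit 3 or 4 to pick up a skin burn, tenderness, edema or fever.

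**The case against.** The strongest case against is that this is one loosely worded sentence plus a preference for more contact. Much of it is fair.

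- A reader might infer that women simply leave one to two hours after the procedure. That is the earliest exit; discharge requires no abnormality, and next-day discharge is allowed.
- A reader might infer that the protocol has no reporting form or time limit at all. It has both, for investigators and for serious events. Section 16.8 also ties the sub-investigator to Section 15.6.3. The gap concerns subjects and ordinary non-serious events.
- A reader might infer that early harms in general rest on recall. Events before discharge are collected at Visit 2, with ultrasound, MRI and observation of the skin. Visit 3 imaging and blood tests can show some later harms. Subjects trained under 15.6.1 may also call in.
- A subject form or instruction may exist in the consent material, which is not at hand. That would answer the question of the form only in part, because 15.6.1 places the time limit in the protocol itself.
- The documents do not say when the listed events usually begin. Several, such as pain, nausea, burns and contrast reactions, could fall within the observed period on the procedure day.
- Safety is summarised descriptively, so no test is invalidated.

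What remains is that post-discharge capture is passive for about two to six weeks, and that the instruction supporting it is incomplete for the people it is meant to guide.

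**Conclusion.** The point holds in a limited form. No contact is scheduled between discharge on the same or next day and Visit 3, at about day 16 to 44 (30-day month assumed; nominally day 30). No physical examination or vital signs are scheduled after the procedure day. Section 15.6.1 leans on a form and a time limit that the protocol does not give to subjects, and no limit covers ordinary non-serious events. Non-serious events that begin after discharge and are not volunteered may therefore rest on recall of up to about six weeks, against the dated detail that 15.6.2 requires.

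It would be tempting to conclude that adverse event counts, durations and severities are biased low by some amount. Under-counting is plausible, but the documents give no onset times and no rate of spontaneous reporting, so neither its size nor its direction can be derived from them. The interval's length describes the calendar, not a share of events lost. This is a cheap improvement to the ascertainment of the only safety endpoint in a single-arm trial, not an error that invalidates the safety analysis.

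**What to change.** Add to the Section 11.5 schedule table (and its copy in the synopsis) and to Section 11.6.2 one scripted telephone contact for adverse events within the first week after the procedure. Base the script on the Section 15.5.1 list, with an open question for anything else, and record the answers on the existing adverse event form in the CRF.

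Reword Section 15.6.1 to separate staff from subjects and to name the form and time limit that apply to a subject's report to the site. A one-page symptom card collected at Visit 3 would be a useful but optional addition.

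This changes data collection only and leaves the discharge and treatment rules as they are. The cost is a protocol amendment with a small CRF change, and about 80 short calls (one for each of 80 subjects) by existing coordinators. The reported count of mild events will probably rise, which the study report should explain as more complete capture.

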**15.6.2. Recording Expected Adverse Events**

When an expected adverse event occurs, the investigator records the following in the CRF.

- Name of adverse event
- Date of onset and resolution
- Severity
- Causal relationship with the investigational medical device
- Treatment details and outcome

**15.6.3. Reporting Serious Adverse Events/Medical Device Reactions**

The investigator shall record all serious adverse events/adverse medical device reactions that occurred during the clinical trial period on a serious adverse event record sheet, and report it to the sponsor within 24 hours regardless of the relationship with the investigational medical device. In this case, in order to protect the ity of the subject's identity, the subject identification code is used in place of the subject's personal information.

In addition, events that suggest significant risks, contraindications, side effects, and precautions that the investigator considers serious or that may be related to the use of investigational medical device are also recorded as serious adverse events/adverse medical device reactions and reported immediately to the sponsor.

When reporting a death case, the investigator must submit additional information such as an autopsy report (applicable only when an autopsy has been performed) and a death certificate to the sponsor and the IRB.

The sponsor shall report serious and unexpected adverse events (including adverse medical device reactions, serious adverse events/adverse medical device reactions) to the Institutional Review Board and the Minister of Food and Drug Safety as soon as possible within the period specified in each of the following subparagraphs.

1. For death or life-threatening cases, the principal investigator must report additional information within 7 days of receiving the report or becoming aware this fact, and in this case, detailed information must be reported within 8 days from the date of the initial report.
2. Any other serious or unexpected adverse events should be reported within 15 days of the principal investigator receiving the report or becoming aware this fact.
3. When a sponsor wishes to report an adverse medical device reaction to the Minister of Food and Drug Safety in accordance with 1) above, it must be submitted in the adverse medical device reaction report according to Form of Attachment No. 36 of the KGCP.

In relation to reporting serious adverse events and adverse medical device reactions, additional safety information should be periodically reported until the relevant adverse reaction is resolved (disappearance of the relevant adverse reaction or lost to follow-up, etc.).

ALPINION Medical Systems Co., Ltd. 37/45

Protocol No. APM-03 Version 1.10/Date 20180103

1. **Measures for Subject Safety Protection**

**16.1. Korean Good Clinical Practice (KGCP) for Medical Device and Declaration of Helsinki**

The procedures stipulated in this protocol are designed to ensure that investigators comply with the basic spirit of the ICH-GCP and the Declaration of Helsinki in conducting, evaluating and recording the results of this clinical trial. This clinical trial will also be conducted in accordance with domestic regulations (Korean Good Clinical Practice, KGCP).

